# Maintenance repetitive transcranial magnetic stimulation (rTMS) therapy for treatment-resistant depression: a study protocol of a multisite, prospective, non-randomized longitudinal study

**DOI:** 10.1186/s12888-023-04944-0

**Published:** 2023-06-16

**Keywords:** Repetitive transcranial magnetic stimulation, Maintenance therapy, Major depressive disorder, Relapse prevention

## Abstract

**Background:**

Repetitive transcranial magnetic stimulation (rTMS) is a widely used treatment for major depressive disorder (MDD), and its effectiveness in preventing relapse/recurrence of MDD has been explored. Although few small sample controlled studies exist, the protocols of maintenance rTMS therapy were heterogeneous and evidence of its effectiveness is not sufficient. Thus, this study aims to evaluate whether maintenance rTMS is effective in maintaining the treatment response in patients with MDD with a large sample size and feasible study design.

**Methods:**

In this multicenter open-labelled parallel-group trial we plan to recruit 300 patients with MDD who have responded or remitted to acute rTMS therapy. Participants would be classified into two groups according to their preference; the maintenance rTMS and pharmacotherapy group, and the pharmacotherapy only group. The protocol of maintenance rTMS therapy is once a week for the first six months and once biweekly for the second six months. The primary outcome is the relapse/recurrence rates during 12 months following enrollment. Other measures of depressive symptoms and recurrence/relapse rates at different time points are the secondary outcomes. The primary analysis is the between-group comparison adjusted for background factors using a logistic regression model. We will perform the group comparison with inverse probability of treatment weighting as the sensitivity analysis to ensure the comparability of the two groups.

**Discussion:**

We hypothesize that maintenance rTMS therapy could be an effective and safe treatment for preventing depressive relapse/recurrence. Considering the limitation of potential bias owing to the study design, we plan to use statistical approaches and external data to avoid overestimation of the efficacy.

**Trial registration:**

Japan Registry of Clinical Trials, ID: jRCT1032220048. Registered 1 May 2022.

**Supplementary Information:**

The online version contains supplementary material available at 10.1186/s12888-023-04944-0.

## Introduction

Major depressive disorder (MDD) is a chronic disorder that is characterized by frequent relapses and recurrences [1]. It is therefore imperative to develop a treatment strategy for maintenance therapy to reduce relapse/recurrence. Although maintenance therapy is commonly provided by pharmacotherapy, approximately half of patients reportedly experience relapse/recurrence even with successfully continued pharmacotherapy [2–4]. Structured psychotherapy, such as cognitive-behavioral therapy and brain stimulation therapy, such as electroconvulsive therapy, have also been explored for their efficacy in preventing relapse/recurrence [5–8]. The recurrence rate has been reported to improve with maintenance therapy using these non-pharmacological therapies in combination with pharmacotherapy, compared to maintenance therapy using pharmacotherapy alone [9–11]. However, considering the limited number of patients for whom these non-pharmacological therapies are indicated and the still high relapse/recurrence rate with the combination therapy, the current treatment options do not fully meet the needs of the patients with MDD.

Repetitive transcranial magnetic stimulation (rTMS) as a brain stimulation therapy is recommended for patients with MDD, especially for those who do not respond to pharmacotherapies [12, 13]. The effectiveness of rTMS therapy in the acute phase has already been demonstrated [14–17]. Recently, the possibility of reducing recurrence/relapse by continuing rTMS therapy in the maintenance phase has been investigated [18–28]. A meta-analysis of the long-term effects of acute rTMS in 732 depressed patients in 18 studies found that the proportion of patients who met the treatment response criteria 6 months later was 61.1% (95% confidence interval: 49.8–71.3%) in the group with and 38.5% (21.9–58.3%) in the group without maintenance rTMS [29]. Although the results seem favorable for maintenance rTMS therapy, owing to the small sample size and the heterogeneity of each study, no definite conclusions can be established concerning the efficacy of maintenance rTMS therapy. Considering the sample size, having a large sample size is challenging in a long-term study, such as maintenance therapy, owing to dropouts and other reasons; thus, it is necessary to adopt a feasible design that facilitates participation in the study. Considering heterogeneity, significant differences, especially in the schedule of maintenance therapy, including weekly (or bi-weekly) rTMS versus clustered rTMS, exist. Prior randomized controlled trials have demonstrated a certain level of effectiveness of clustered rTMS as maintenance therapy, with the advantage of reducing the number of hospital visits [30]; however, concerns remain about adverse events, since a greater amount of stimulation is performed in a shorter period of time. Although some case reports and small sample studies exist [18, 28, 31], the efficacy and safety of maintenance treatment with weekly or bi-weekly rTMS therapy remain unknown.

We hypothesized that a weekly or biweekly maintenance rTMS therapy schedule could be effective in preventing depressive relapse/recurrence. Thus, the main objective of this study was to evaluate the efficacy and safety of 12 months of maintenance rTMS therapy in patients with moderate to severe treatment-resistant MDD who respond to acute rTMS therapy with a feasible study design.

## Materials and methods

### Study overview

This study is a multisite, prospective, non-randomized longitudinal trial, recruiting 300 participants, who will be divided into two groups: (I) the maintenance rTMS plus pharmacotherapy group and (II) the pharmacotherapy-only group. The overview of the study is shown in Fig. 1. Only patients who achieve a therapeutic response to acute rTMS therapy will be included in the study. In the maintenance rTMS plus pharmacotherapy group, patients will receive weekly treatments for 6 months, followed by bi-weekly treatments for an additional 6 months, totaling 12 months of maintenance rTMS therapy (maximum 40 sessions). During the maintenance period, the patient will continue with a stable dose of pharmacotherapy. In the pharmacotherapy-only group, patients will receive no intervention other than a continuation of concomitant pharmacotherapy and receive an evaluation. Assessments will be made at 3, 6, 9, and 12 months after the start of maintenance therapy and at the end of study participation. Random allocation to both the groups will not be performed and the patients will be classified to a group (I) or (II) according to their preferences. Owing to the long duration of maintenance therapy immediately following acute treatment in this study, conducting a double-blind, randomized, sham-controlled, parallel-group study was deemed challenging in terms of subject participation and blinding validity.

**Fig. 1 Fig1:**
[figure not shown]
Flowchart of the study. rTMS: repetitive transcranial magnetic stimulation

The National Center of Neurology and Psychiatry Clinical Research Review Board approved the study protocol (approval number: CR21-004) following the principles of the Declaration of Helsinki. The approval encompasses all participating centers in accordance with the Clinical Trials Act in Japan. The trial has been registered in the Japan Registry of Clinical Trials (ID: jRCT1032220048, final update is protocol version 2.0, 1 May 2022). Independent quality monitoring of the trial will be performed in order to ensure the quality of the study. Written informed consent will be obtained from all the participants before beginning the study.

### Participants

#### Inclusion criteria

Participants with MDD above the age of 18 years who responded or remitted to 3–6 weeks of acute rTMS therapy will be included. In Japan, rTMS is indicated for patients who have failed to respond to at least one or more antidepressants; thus, these patients will be included in this study. All the participants must understand and be willing to adhere to the 12-month maintenance therapy schedule. The researchers will obtain informed consent from the participants who meet the criteria.

#### Exclusion criteria

Possible pregnancy, significant suicidal ideation (suicide item score of Hamilton Rating Scale for Depression 17 item (HAMD-17) ≥ 3), and severe side effects from acute rTMS therapy are the exclusion criteria for this study. Patients with an intracranial implant (e.g., cochlear implants, magnetic clips, stimulators, such as deep brain stimulators) or other metal objects near the stimulation site (e.g., cardiac pacemakers) are contraindicated for rTMS therapy and therefore, patients with these conditions are not eligible for this study.

#### Power and sample size calculation

In the previous meta-analysis of maintenance rTMS therapy, the response rates at 3 and 6 months in the group with and without maintenance rTMS therapy were 76.2% and 61.1%, and 56.1% and 38.5%, respectively [29]. Applying the Weibull distribution to the 3- and 6-month response rates, the 12-month response rate was estimated to be 40.9% for the maintenance rTMS group and 20.7% for the no maintenance rTMS group, with an estimated difference of 20%. Considering the relapse and recurrence rates, the previous randomized controlled trial of maintenance therapy in patients who responded to pharmacotherapy reported 44.4% in the pharmacotherapy-only group and 24.2% in the rTMS maintenance therapy group, with a 20.2% difference between the groups [30]. Based on these previous studies, we estimated that the relapse/recurrence rate without maintenance rTMS was 45–60%, and the add-on effect of maintenance rTMS was 20%. To detect a 20% additional effect of maintenance therapy, the required sample size varies from 109 to 130 patients for a 45 ~ 60% relapse/recurrence rate in the pharmacotherapy-only group (chi-squared test with two-sided alpha = 0.05 and power = 80%). Since this study plans to conduct a multivariable analysis adjusting for the background factors, the power was set as high as 90%. Assuming that the proportion of participants who drop out without any evaluation of efficacy is 15%, the required number of participants would be 150 in each group.

From the viewpoint of detection of rare adverse events in the maintenance rTMS group, with 150 participants, at least one event with a 2% probability with a 95% chance is expected. Therefore, based on the perspective of comparing the efficacy and collecting safety information, the target number of study participants was set at 150 in each group, with a total of 300 participants.

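### The printed requirement of 109 to 130 patients at 80% power does not reproduce: the stated inputs give 89 to 97 per group at 80% and 118 to 130 at 90%, so the power label and the lower figure need correcting, though 150 per group stands

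*Protocol article*

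**What the plan says.** All the figures are in the protocol article, under Power and sample size calculation.

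- **Rates and effect:** "we estimated that the relapse/recurrence rate without maintenance rTMS was 45–60%, and the add-on effect of maintenance rTMS was 20" percent. Two sources precede this: extrapolated response rates ("the 12-month response rate was estimated to be 40.9% for the maintenance rTMS group and 20.7% for the no maintenance rTMS group") and an earlier randomised trial with relapse rates of 44.4% and 24.2%.
- **Requirement:** "the required sample size varies from 109 to 130 patients", with the method given in brackets as "chi-squared test with two-sided alpha = 0.05 and power = 80" percent.
- **Power of the design:** because the analysis will adjust for background factors, "the power was set as high as 90" percent.
- **Final size:** with 15% lost without any efficacy evaluation, "the required number of participants would be 150 in each group".

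Two other sections bear on the point. The primary analysis is a multivariable logistic regression (Statistical analysis, Primary outcome). Groups are not randomised: "the patients will be classified to a group (I) or (II) according to their preferences" (Study overview).

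**The concern.** The paragraph gives two power levels and one range of sample sizes. The range is tied to 80%, the design is said to have 90%, and no second range is given for 90%. If 109 to 130 were truly the 80% requirement, moving to 90% and adding 15% for dropout would take the trial well past 150 per group. If 109 to 130 is already the 90% requirement, the label is wrong and 150 follows. A reader cannot tell which without redoing the calculation, and this paragraph is the efficacy justification for enrolling 300 patients.

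The reason given for 90% also matters. It is offered as the allowance for covariate adjustment, so readers should be able to see what size it produced and whether anything was added on top.

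**Working it through.** **Inputs, all from the power paragraph:** two-sided alpha 0.05 (z = 1.960); power 80% (z = 0.842) or 90% (z = 1.282); control rate p1 from 0.45 to 0.60; p2 = p1 − 0.20; dropout 15%. The printed range is read as per group, because the final target is per group. Read as a total it would be 55 to 65 per group, which fits still less well.

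**Formula** (chi-squared test, equal groups, p̄ the mean of p1 and p2):

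n per group = [z(α/2)·√(2p̄(1−p̄)) + z(β)·√(p1(1−p1) + p2(1−p2))]² / (p1−p2)²

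**Step 1: the printed range at the printed 80% power.**
- 45% vs 25%: [1.960·√0.455 + 0.842·√0.435]² / 0.04 = 88.1, so 89.
- 60% vs 40%: [1.960·√0.500 + 0.842·√0.480]² / 0.04 = 96.9, so 97.

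The result is 89 to 97, not 109 to 130. Other standard versions at 80% do not reach it either: continuity-corrected 98 to 107, unpooled variance 86 to 95, arcsine 88 to 97, one-sided 70 to 77.

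**Step 2: the same at 90% power.**

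| Control vs rTMS | n per group, 90% |
|---|---|
| 45% vs 25% | 117.4, so 118 |
| 50% vs 30% | 124 |
| 55% vs 35% | 128 |
| 60% vs 40% | 129.3, so 130 |

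The upper printed figure is matched exactly. The lower is not: 45% vs 25% needs 118, and 109 per group would give 87.7% power there.

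**Step 3: where 109 could come from.**
- 40% vs 20% at 90%: [1.960·√0.42 + 1.282·√0.40]² / 0.04 = 108.2, so 109. This control rate is outside 45% to 60%.
- The quoted response rates, 40.9% vs 20.7%, at 90%: 108.
- The quoted relapse rates, 44.4% vs 24.2%, at 90%: 114.

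A plausible origin is the response-rate pair rounded to 40% vs 20%, but the article does not say so, and its sentence refers to relapse/recurrence rates.

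**Step 4: the literal reading.** Going from 80% to 90% power multiplies n by about (1.960 + 1.282)² / (1.960 + 0.842)² = 1.339.
- 109 × 1.339 = 146; 146 / 0.85 = 172.
- 130 × 1.339 = 174; 174 / 0.85 = 205.

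That is 172 to 205 enrolled per group, against 150 planned.

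**Step 5: the 90% reading.**
- 118 / 0.85 = 139 and 130 / 0.85 = 153 enrolled per group.
- 130 × 1.15 = 149.5, which rounds up to the stated 150. Dividing by 0.85, the usual inflation, gives 153, a difference of three patients.
- 150 × 0.85 = 127.5. With 127 evaluable per group, unadjusted power is 92.1% (45% vs 25%) and 89.5% (60% vs 40%).

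**The case against.** The strongest reply is that the design is sound. On the only reading that fits the final number, 150 per group gives about 90% power, so this is a reporting slip that changes nothing in the conduct of the trial. That stands, and it limits the point to the wording. It does not remove it: the printed power is wrong for the printed range, and the printed lower bound is wrong at either power.

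It can also be said that 109 is not arbitrary, being within two patients of the 90% answer for the quoted response rates. That is fair as an explanation. The sentence still ties the figure to control relapse rates of 45% to 60%, which it does not fit.

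A reader might infer more, and the document does not support it:

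- **That the trial is too small.** The 172 to 205 per group holds only if the 80% label is right, and Steps 1 and 2 show it is not.
- **That the adjusted primary analysis lacks 90% power.** The document gives no figure for how strongly covariates predict group. If they explained 5% of group membership (an assumption), the simple reduction of n by that share gives 88.0% to 90.9%; at 10% it gives 86.3% to 89.3%. That method ignores any gain from prognostic covariates. Whether adjusted power lies above or below 90% cannot be determined.
- **That preference will unbalance the groups enough to matter.** The target is 150 in each group. An assumed 1.5:1 split of 255 evaluable still gives 88.4% to 91.3%. Larger imbalances cost more, but nothing in the document predicts them.
- **That the safety statement is wrong.** It is already tied to 150 rTMS patients, and 1 − 0.98^150 = 95.2%, as claimed.

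**Conclusion.** The sample-size statement is wrong as printed in two places. The range labelled 80% power is not an 80% range: the stated inputs need 89 to 97 per group. At 90% power they need 118 to 130, so the upper figure is right for 90% and the lower is 9 patients too small for 45% vs 25%. The paragraph also contradicts itself, because its literal sequence leads to 172 to 205 per group rather than 150.

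The consequence is confined to reporting. Read as 118 to 130 at 90% power, the plan needs 139 to 153 enrolled per group, and 150 is adequate within rounding, with about 89.5% to 92% power. These results use only the article's own inputs, the standard chi-squared formula, equal groups and 15% loss. They describe the unadjusted test. Choosing 90% rather than 80% is the only margin for covariate adjustment; the stated size contains no separate allowance beyond it.

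**What to change.** Replace the requirement and power sentences with a statement to this effect:

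> For control relapse/recurrence rates of 45% to 60% and an absolute reduction of 20 points, 118 to 130 evaluable patients per group give 90% power (unadjusted chi-squared test, two-sided 5%, equal groups). Allowing for 15% loss, this is 139 to 153 enrolled per group. With 150 per group (about 127 evaluable), power is about 89.5% to 92%. This is the power of the unadjusted test at an equal split; no separate allowance for the covariate-adjusted primary analysis is included.

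If 109 was derived from the response rates, either remove it or label it as such. The sample size, the analysis and the safety detection statement need no change. The cost is rewording one paragraph, plus a power figure that is marginally below 90% at the top of the control-rate range.

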### RTMS protocol

All the rTMS treatment will be performed using the NeuroStar TMS system (Neuronetics, Inc., Malvern, PA, USA) at a 120% resting motor threshold over the left prefrontal cortex at 10 Hz, with a 4-s stimulation time, 11-s or 26-s inter-stimulation interval, and 3000 pulses/day. The left prefrontal cortex stimulation site was determined by advancing the coil 5.5 cm anterior to the motor threshold location. In the event of problems caused by rTMS therapy stimulation, such as headache, move the coil within 0.5 cm of the stimulation site or rotate it -5 to + 5 degrees around the coil intersection to alleviate symptoms. Participants will be excluded from the intervention if they exhibit unacceptable adverse reactions, are diagnosed with mania or hypomania, or exhibit symptoms that would preclude them from continuing with the trial. Therapists will be in close contact with the participants to increase adherence to the intervention.

Acute-phase rTMS treatment prior to inclusion in this study will be performed as per usual practice in accordance with the Japanese guidelines for the appropriate use of rTMS [32]. Treatment will be administered once daily for up to five days a week, for a maximum duration of six weeks. If patients meet the remission criteria or conversely do not obtain therapeutic effect at the end of three weeks of the treatment, rTMS treatment will be discontinued or gradually tapered off over the course of an additional three weeks. Alternatively, treatment will be continued for 6 weeks. The patients will be administered a stable dose of psychotropic medications during the treatment period.

### Covariates and outcomes

An overview of the schedule of assessments is shown in Table 1. To ensure the reliability of the assessment, the HAMD-17 and Montgomery–Åsberg Depression Rating Scale (MADRS) will be conducted by clinical or licensed psychologists who have experience in clinical trials. Before the start of the study, we will confirm the agreement of the ratings by using a simulated patient using video clips. In principle, the same evaluator will conduct the evaluation for each participant. In this study, the response is defined as a decrease of 50% or more in the total HAMD-17 score compared to that before the acute phase of rTMS therapy. Remission is defined as a HAMD-17 total score ≤ 7. Relapse/recurrence is defined as a total HAMD-17 score ≥ 14. Cohen's d will be calculated to evaluate the magnitude of the treatment effect for each outcome.

**Table 1 Tab1:** Assessment schedule

	Screening period	Maintenance therapy period				
	1 week	12 months				
	-1 week	0 month	3 month	6 month	9 month	12 month
Screening	◯					
Informed consent	◯					
Patients back ground	◯					
Maintenance rTMS		—△ →	—△ →	—△ →	—△ →	—△ →
Concomitant medications use		★	★	★	★	★
Adverse events		★	★	★	★	★
HAMD-17		◯	◯	◯	◯	◯
MADRS		◯	◯	◯	◯	◯
QIDS		◯	◯	◯	◯	◯
PHQ-9		◯	◯	◯	◯	◯

*HAMD* Hamilton Rating Scale for Depression, *MADRS* Montgomery–Åsberg Depression Rating Scale, *QIDS* Quick Inventory of Depressive Symptomatology, *PHQ-9* Patient Health Questionnaire-9

△: only for maintenance rTMS plus pharmacotherapy group

★: concomitant medication use and adverse events are assessed at each treatment session or outpatient visit

Primary outcome
Relapse / recurrence rates during 12 months after enrollmentSecondary outcome measuresRelapse / recurrence rates at 3, 6, and 9 months after enrollment (Those who have met the criteria for relapse/recurrence prior to each evaluation period will be treated as relapse/recurrence thereafter.Response rate at 3, 6, 9, and 12 months after enrollmentRemission rates at 3, 6, 9, and 12 months after enrollmentChanges in the HAMD-17, MADRS, Quick Inventory of Depressive Symptomatology (QIDS), and Patient Health Questionnaire-9 (PHQ-9) scores since enrollmentTime to relapse/recurrence after enrollmentAdverse events and equipment failure (headache, pain or irritation at the site of stimulation, manic and hypomanic episodes that meet the diagnostic criteria of Diagnostic and Statistical Manual of Mental Disorders, 5th edition (DSM-5), suicide ideation, seizure, etc.)Other covariates
Demographic characteristics and clinical observation information (information obtained from interviews and medical records, including sex, age, comorbidities, and duration of illness)Reasons for treatment selection (confirm reasons for choosing to do or not to do maintenance rTMS therapy in multiple-choice and free-text format)

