### Data collection and data management

All the evaluations will be conducted by experienced psychologists. After the data are collected, all the data in the paper files will be transcribed to the Electronic Data Capture system (e Clinical Base; Translational Research Center for Medical Innovation, Kobe, Japan), which is a secure system designed for storage of personal and patient data. The data will be sent to independent data managers to assess whether the data were collected properly, focusing on the status of consent acquisition, eligibility of the participants, evaluation items, and confirmation of drop-out/terminated cases. These data managers will also oversee and review the progress of the trial. If a participant withdraws their consent, they will be dismissed from the study. At the same time, we will record the dropout rate, and the number of participants with adverse events requiring treatment. The Efficacy and Safety Assessment Committee, whose members are independent of the research, will check and assess whether the trial is conducted safely and properly, and will also decide whether to stop the trial if any severe adverse events or protocol violations occur. In addition, an on-site data monitor will conduct monitoring to ensure that the trial is performed properly, data are properly recorded, and data reliability is ensured. Audits will be also conducted independent of the researcher and sponsor. If we conduct any necessary protocol modifications, we will report them to the Clinical Research Review Board, and to the registration site of the Japan Registry of Clinical Trials website. The results of this study will be anonymized and published in relevant academic conferences and journals.

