Considering feasibility and blinded validity, conducting this study as a double-blind randomized controlled trial is challenging. The total number of sessions in this study is 40 and the duration of maintenance therapy is 12 months, which is considered to be a significant burden for the participants assigned to sham stimulation owing to a large number of sessions and the long duration of the study. Moreover, since all the participants in this study received acute rTMS therapy before entering the maintenance rTMS therapy period, patients may be able to distinguish between real and sham stimulation, which would reduce the blinded validity of the study. Thus, an open-label, nonrandomized study design will be employed in this study.

As mentioned before, the risk of bias owing to the lack of blinding and randomization is a limitation of this study. For example, patients who are favorable to rTMS therapy may be more likely to be assigned to the maintenance rTMS group, resulting in a larger placebo effect and overestimating the effect of maintenance rTMS therapy. We plan to address this point in two ways. The first is to adjust for the background factors by performing IPTW analysis as a sensitivity analysis and attempting to increase the two groups' comparability. However, risk of bias remains because unmeasured confounding cannot be eliminated by an IPTW analysis. Second, the long-term outcome of post-marketing surveillance of the Nerurostar TMS device in Japan will be used as a historical control. Comparing the maintenance therapy group with both the control group in this study and the historical control group may reduce the possibility of overestimating the effect of treatment.

If maintenance rTMS is shown to be effective in preventing relapse/recurrence of depression in this study, the treatment options for patients who have had difficulty maintaining remission with antidepressants and/or psychotherapy will be expanded. Since rTMS is a developing technology, there is no evidence that the current stimulation protocol is the best for treating patients with MDD. The search for optimal protocols for rTMS maintenance therapy and updates to accommodate new rTMS stimulation methods, which are being improved daily, should be continued in future studies.

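### The primary endpoint is a psychologist-rated HAMD-17 cut-off in an open-label study; the article describes no rater masking, and neither stated bias remedy can correct group-dependent rating

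*Protocol article*

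**What the plan says.** **Design.** Study overview: "the patients will be classified to a group (I) or (II) according to their preferences". Discussion: "Thus, an open-label, nonrandomized study design will be employed in this study".

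**Endpoint and raters.** Covariates and outcomes: "Relapse/recurrence is defined as a total HAMD-17 score ≥ 14". The primary outcome is the proportion relapsing within 12 months, with assessments at 3, 6, 9 and 12 months. HAMD-17 and MADRS "will be conducted by clinical or licensed psychologists who have experience in clinical trials". Data collection and data management repeats this: "All the evaluations will be conducted by experienced psychologists". Two further rating safeguards are given: an agreement check on video before the study starts, and "In principle, the same evaluator will conduct the evaluation for each participant".

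**Bias.** The Discussion states that "the risk of bias owing to the lack of blinding and randomization is a limitation of this study". It gives the example of patients who favour rTMS choosing maintenance and showing a larger placebo effect, and then lists two measures. "The first is to adjust for the background factors by performing IPTW analysis as a sensitivity analysis"; the second is a historical control from post-marketing surveillance. It concedes that IPTW leaves unmeasured confounding. The Abstract presents statistical approaches and external data as the means of avoiding overestimated efficacy.

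**The concern.** HAMD-17 is scored by an interviewer, and the primary event is one cut on that score. If the interviewer knows the group, a small leniency for patients still receiving rTMS turns some scores of 14 or 15 into 13, and each such change can remove a primary event. The error arises after the group is chosen and lies in the outcome itself, so no adjustment for baseline covariates can detect or remove it.

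Wherever the article discusses blinding, it means sham stimulation and whether patients would recognise it. Masking the outcome raters needs no sham and is not considered. What is at stake is an apparent relapse benefit that comes partly from the measurement and that the planned sensitivity analyses would leave in place.

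**Working it through.** **1. What each stated measure acts on**

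| Measure | Acts on | Effect on group-dependent rating |
|---|---|---|
| Rater experience, video agreement check, same evaluator | Reliability between and within raters | None: raters can agree on a video and still score differently when they know the group |
| IPTW (Sensitivity analysis) | Balance of baseline covariates: age, sex, episodes, duration, medication, status at enrollment | None: the outcome value is weighted, not corrected |
| Censoring weights (Sensitivity analysis) | Informative dropout | None |
| Historical control | Choice of comparator | None: the maintenance group keeps the same ratings, and the Historical control section does not say who rates the surveillance patients or by what relapse criterion |

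**2. The plan's own sample size, to fix the inputs**

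A pooled chi-squared test, two-sided 0.05, 90% power, 60% against 40%, needs 130 per group. Then 130 / 0.85 = 153, or 130 × 1.15 = 149.5, rounded to the stated 150. The evaluable number is 150 × 0.85 = 127.5 per group.

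**3. Size of a rating shift (illustration)**

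From the protocol: control relapse p = 45 to 60%, planned effect 20 points, 127.5 evaluable per group. Assumed, because the documents give neither: a normally distributed score with SD 5 to 7, and a shift of s points lower in the maintenance group with no true treatment effect.

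Recorded rate in the maintenance group: p2 = 1 − Φ(z + s/SD), where z = Φ⁻¹(1 − p).

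Example, p = 0.45, SD 5, s = 1: z = 0.126, so p2 = 1 − Φ(0.326) = 0.372, and the fall is 0.450 − 0.372 = 0.078.

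Rejection probability of the unadjusted test: Φ((b − 1.96·se0)/se1) + Φ((−b − 1.96·se0)/se1), with b = p − p2, se0 from the pooled rate and se1 from the two separate rates. In the example se0 = 0.0616 and se1 = 0.0614, so the first term is Φ((0.0777 − 0.1208)/0.0614) = Φ(−0.70) and the sum is 0.242.

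| Shift | Fall in recorded relapse, p = 45 to 60%, SD 7 to 5 | Rejection with no true effect |
|---|---|---|
| 0 | 0 | 5% |
| 0.5 point | 2.8 to 3.9 points | 7 to 10% |
| 1 point | 5.6 to 7.9 points | 15 to 24% |
| 2 points | 11.0 to 15.8 points | 43 to 72% |

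A 1-point shift is therefore 5.6/20 = 28% to 7.9/20 = 40% of the planned effect.

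**4. Sensitivity to the simplifications**

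- *Four visits.* The endpoint is any relapse over four assessments. Simulating any-of-four crossing, with an assumed within-patient correlation of 0.5 to 0.7 and a 1-point shift, gives a fall of about 6 to 9 points and about 17 to 31% rejection.
- *Lower true rate.* At a true maintenance relapse rate of 25%, the single-visit formula with s = 1 gives 0.059 (SD 5) to 0.043 (SD 7), about 4 to 6 points.

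Masking the raters changes no sample-size input, so 150 per group stands.

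**The case against.** **The article is silent on masking.** A reader might infer that the raters know the group, or that the plan has them rate unmasked. The documents do not support that. No sentence says so, the full protocol is not shown, and it may provide for masked rating. This stands, and the fix is conditional on it.

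**The Discussion does not claim to cure rater bias.** The two measures follow directly on the example of preference and placebo effect, and that is their nearest referent. The text also concedes residual bias and says only that the historical comparison may reduce overestimation. It would go too far to say that the article asserts IPTW corrects ratings. What remains is narrower: lack of blinding is named as a source of bias, and nothing offered acts on the rating part of it.

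**Separation of raters and therapists is inferred.** Psychologists rate, a physician examines after each stimulation, and therapists are mentioned without a profession. No sentence excludes psychologists from delivering rTMS. The fix therefore has to state the separation.

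**Self-ratings are already there.** QIDS and PHQ-9 are planned secondary outcomes. A reader might take them as a check on rater bias, but patients who know their group complete them, so they are not a masked check.

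**The change is not free.** The trial is ongoing and keeps one evaluator per participant. A rater who already knows a participant's group cannot be made unaware of it.

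**The magnitude is hypothetical.** The SD and the shift are both assumed. The figures show how sensitive the endpoint is, not that bias is present.

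**Conclusion.** The point holds in a limited form. The primary endpoint is a rater-scored threshold in an open-label, preference-allocated study. The article describes no masking of raters, and neither IPTW nor the historical control can correct rating that differs by known group. The Abstract's aim of avoiding overestimation is therefore not met for observer bias, although lack of blinding in general is disclosed as a limitation.

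On size, a 1-point differential would account for roughly 6 to 8 of the planned 20 points. That rests on an assumed SD of 5 to 7, a single-visit normal model and 45 to 60% control relapse; the range is somewhat higher over four visits and lower at a 25% relapse rate. Whether any differential exists cannot be known from the document.

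Masked raters would remove observer bias only. Patient expectation and preference-based confounding would remain. This is a worthwhile, low-cost improvement, and it does not invalidate the design.

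**What to change.** 1. If the full protocol already masks the raters, say so in the published description. If not, require for all remaining assessments that the psychologists rating HAMD-17 and MADRS take no part in rTMS delivery and are not told the group, and that patients are asked not to reveal it.
2. Record any unmasking, or a rater's guess of group, and flag every rating made before the change so that the two rating conditions can be told apart in the analysis.
3. Reword the Discussion so that IPTW and the historical control are presented as addressing preference-related confounding only, with residual observer bias and patient expectation stated as limitations. Bring the Abstract into line.
4. Keep QIDS and PHQ-9 as planned, and do not describe them as a masked check.

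**Cost.** No extra staff and no change to sample size, endpoint or treatment. It needs site instructions, one form item, care in scheduling, and a modification reported to the review board and the registry. Some accidental unmasking will occur, more likely because one evaluator follows each participant for 12 months, and participants already enrolled will have mixed rating conditions.
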